## Aims and hypotheses

### Main Aim: To evaluate the efficacy of the Facebook-based intervention for young adults in a randomized controlled trial

Hypotheses are:Participants receiving the intervention will have higher 7-day point prevalence abstinence at 3-, 6-, and 12-months follow-up compared to those in the control condition.Participants in the intervention condition will demonstrate greater reduction in cigarettes smoked and increased commitment to abstinence at 3-, 6-, and 12-months follow-up than those in the control condition.Participants in the intervention condition will be more likely to make a quit attempt during the 12-month study period compared to those in the control condition.

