## Methods/Design

### Overview of design

This study is a randomized controlled trial (RCT) with 480 young adults age 18 to 25 recruited through Facebook (Fig. 1). Participants are randomized to one of two conditions: (1) the Tobacco Status Project motivationally-tailored smoking cessation intervention delivered through Facebook (TSP); or (2) a control condition (referral to the Smokefree.gov website). Assessments are conducted online at baseline, 3-, 6-, and 12-months follow-up. Primary outcome is biochemically-verified 7-day point prevalence abstinence from tobacco, and secondary outcomes are reduction in cigarettes smoked per week, 24 h quit attempts, and commitment to abstinence in each time period. Within the TSP group, a monetary engagement will be tested as a moderator of engagement and abstinence.

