### Secondary outcomes

The following secondary outcomes will be assessed at each timepoint:**Reduction of cigarette consumption by 50 % or more (y/n)** between baseline each follow-up will be calculated from the number of cigarettes smoked in the past 7 days at each time point.**Tobacco quit attempt** (y/n). A *Follow-up Smoking Questionnaire* will assess the presence and number of 24 h quit attempts since the last assessment, used to calculate presence of at least one quit attempt in the assessment time period.**Readiness to quit tobacco** will be assessed using the *Stages of Change Questionnaire*, [44] categorizing participants into five stage categories at each timepoint (precontemplation, contemplation, preparation, action, and maintenance), and predictive of quit attempts and cessation [51]. Outcome will be measured as proportion in action or maintenance stage sof change at 3, 6, and 12 month assessments.**Abstinence goal** will be assessed with the *Thoughts About Abstinence Form, *[52]*,* categorizing goal as no goal, intermediary goal (e.g., reduced smoking), or total abstinence. Outcome will be measured as proportion endorsing a goal of abstinence at each timepoint.**Engagement in TSP** will be measured by total number of comments to Facebook study groups during the three-month intervention period.

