### Secondary analyses

Mixed effects logistic and multinomial regression models for longitudinal ordinal response data to model secondary outcomes for tobacco use and across time (3, 6, 12 months): 1) reduction of cigarettes by 50 % or more (y/n), 2) tobacco quit attempt (y/n; 2 models), 3) action or maintenance stage of change (y/n); and 4) commitment to abstinence (y/n). Independent variables in all models will be treatment condition, abstinence status, and covariates identified as relevant to smoking characteristics in the literature.

To evaluate the secondary aim (effect of a monetary incentive on engagement in the TSP condition), we will test for differences in engagement and primary smoking outcome by incentive groups and the relationship between engagement and primary smoking outcome at 3 months. First, due to expected skewed distribution of the engagement variable (comments), the non-parametric Kruskal-Wallace test will examine overall differences in total number of comments made to the Facebook study group by incentive condition, with test for a linear trend in commenting by incentive frequency. Second, Pearson’s chi-square test will examine 7-day point prevalence abstinence by incentive condition. Abstinence rates will be examined by incentive group. Two sets of analyses will be conducted: one for biochemically verified abstinence, and one for reported abstinence. Finally, Mann–Whitney U tests will compare comments for those abstinent at 3months to those non-abstinent. Again, two sets of analyses will be conducted (one for biochemically-verified abstinence and one for reported abstinence).

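### The quit-attempt hypothesis covers the whole 12 months, but the stated outcome and models are per interval and adjusted for abstinence, and no stated endpoint matches the hypothesis

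*Protocol article*

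**What the plan says.** All references are to the protocol article.

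- **Aims and hypotheses, Main Aim.** The third hypothesis is that intervention participants "will be more likely to make a quit attempt during the 12-month study period compared to those in the control condition". That is one event per person over one year.
- **Overview of design.** Assessments: "Assessments are conducted online at baseline, 3-, 6-, and 12-months follow-up". The secondary outcomes listed there include "24 h quit attempts, and commitment to abstinence in each time period".
- **Secondary outcomes.** The follow-up questionnaire "will assess the presence and number of 24 h quit attempts since the last assessment", and this is "used to calculate presence of at least one quit attempt in the assessment time period".
- **Secondary analyses.** Mixed-effects models across 3, 6 and 12 months are planned for a list of outcomes that includes "tobacco quit attempt (y/n; 2 models"; what the two models are is not said. On the terms in them: "Independent variables in all models will be treatment condition, abstinence status, and covariates identified as relevant to smoking characteristics in the literature".

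No section defines an any-attempt-by-12-months variable, and none says how a participant who is already abstinent when an interval starts, and stays so, is coded for that interval.

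**The concern.** The hypothesis and the outcome are different quantities. One asks whether a person ever tried during the year. The other asks, three times, whether the person tried since the previous survey.

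They diverge most for the participants who did best. A smoker who quits in month 2 and never relapses reports an attempt at 3 months and, taking the question at its word, none at 6 or 12 months. At those two assessments this person looks the same as a smoker who never tried. If the intervention produces more sustained quitters, as the first hypothesis expects, it also collects more of these negative answers.

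Adjusting for abstinence status does not restore the hypothesised comparison. Abstinence arises after randomisation and is itself expected to differ by arm, so the adjusted treatment term is no longer the effect of assignment on making an attempt. It also relates to attempts in opposite ways over time. At 3 months, abstinence in someone who smoked at entry nearly always follows an attempt; at 6 and 12 months, sustained abstinence means no new one. Nor does 7-day abstinence at a visit identify who was abstinent throughout the interval.

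At stake is the interpretation of one of the three main-aim hypotheses. The primary abstinence outcome is not touched.

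**Working it through.** The article states no rate, sample size or power for quit attempts, so there is no figure of its own to reproduce. The check has two parts.

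**1. Trace one participant through the stated rule.** All participants smoke at entry (Inclusion criteria). Take one who quits before month 3 and does not smoke again.

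| Interval (months) | New attempt in interval | Literal per-interval code | Any attempt so far |
|---|---|---|---|
| 0-3 | yes | yes | yes |
| 3-6 | none | no | yes |
| 6-12 | none | no | yes |

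The last column answers the hypothesis. The third column does not, except at 3 months. The three intervals together cover the full year, so the last column can be derived from data already planned. The last interval is also twice as long as each of the first two.

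**2. Illustrate the direction and possible size at 6 or 12 months.**

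Inputs:
- q, the share abstinent throughout the interval: 10% intervention, 5% control. These are the planning rates under Power calculation, which are 7-day point prevalence. Using them as sustained shares is an assumption, and the sustained share can only be equal or smaller.
- a, the share of the remaining participants who attempt in the interval: assumed, 30% to 60%, equal in both arms. The feasibility trial's 67% (Background) covers baseline to 12 months and is not an interval rate.

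Formulas:
- literal coding: (1 - q) × a
- sustained quitters credited: q + (1 - q) × a

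| a | Literal, intervention vs control | OR | Credited, intervention vs control | OR |
|---|---|---|---|---|
| 30% | 27.0% vs 28.5% | 0.93 | 37.0% vs 33.5% | 1.17 |
| 40% | 36.0% vs 38.0% | 0.92 | 46.0% vs 43.0% | 1.13 |
| 50% | 45.0% vs 47.5% | 0.90 | 55.0% vs 52.5% | 1.11 |
| 60% | 54.0% vs 57.0% | 0.89 | 64.0% vs 62.0% | 1.09 |

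Example, a = 40%: literal 0.90 × 0.40 = 0.360 and 0.95 × 0.40 = 0.380; credited 0.10 + 0.360 = 0.460 and 0.05 + 0.380 = 0.430.

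With equal a, the literal difference is -(10% - 5%) × a and the credited difference is +(10% - 5%) × (1 - a), so both shrink in proportion if the sustained shares are smaller.

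Varying the assumptions:
- The intervention also raises attempts among the rest, a = 60% vs 50%, same q: literal 54.0% vs 47.5%, OR 1.30; credited 64.0% vs 52.5%, OR 1.61. The literal coding weakens the effect but does not reverse it.
- The higher rates quoted under Power calculation, q = 20% vs 9%, with a = 50% in both arms: literal 40.0% vs 45.5%, OR 0.80; credited 60.0% vs 54.5%, OR 1.25.

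All of these are unadjusted comparisons. On the equal-a numbers, the attempt rate is a in both arms among the others and zero in both arms among sustained quitters. A comparison adjusted for sustained abstinence would therefore show no difference, rather than one favouring control.

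**The case against.** The strongest counter-case has five parts.

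**The coding of an ongoing quit is inferred.** A reader might conclude that the plan codes sustained quitters as having made no attempt. The article does not say so. The questionnaire items are not shown, and item wording and derivation rules are what an article leaves to fuller documents. This stands: the consequence above is the literal reading, not a documented rule.

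**The hypothesis may still be tested.** A reader might conclude that the 12-month hypothesis goes untested. That is too strong. The intervals span the year, the outcome is modelled at all three assessments, and one of the two unexplained models could be cumulative. What remains is that no stated endpoint or model matches the hypothesis.

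**The reversal is built from assumptions.** It treats point prevalence as sustained abstinence, sets equal attempt rates in the rest (contrary to the hypothesis) and leaves out the planned adjustment. Its size is also modest: at a = 40% the gap is 2 points, with a standard error of √[(0.36 × 0.64 + 0.38 × 0.62)/240] = 4.4 points if 240 per arm are analysed. This stands too. A reversed result is possible, not shown.

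**Assessment point.** Its absence from the list of terms may be condensed wording, since the models are described as longitudinal and the primary model includes it. It carries little weight here.

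**An interval attempt is a coherent endpoint, and crediting abstinence mixes it with the primary outcome.** True for an endpoint chosen for its own sake. It does not make the interval outcome the one hypothesised. In a cumulative variable the sustained quitter already counts through the 3-month report, if that survey was completed.

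**Conclusion.** The concern holds in limited form. The article fixes a 12-month hypothesis in one section and a per-interval outcome, adjusted for post-randomisation abstinence, in the others. This is a mismatch between statements the article makes, not detail left for another document.

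On the literal wording, the 6- and 12-month comparisons can be pulled against an arm with more sustained quitters. The direction follows whenever sustained quitting differs between arms; the size cannot be known from the documents. In the illustration, with equal attempt rates among the rest, the unadjusted odds ratio lies slightly below 1 with literal coding and slightly above 1 when quitters are credited. The coding problem cannot arise at 3 months, though the adjustment for abstinence still applies there.

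The documents do not support saying that the planned analysis will favour control. That would need the literal coding to be what is done, no effect on attempts among the others, and no adjustment.

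**What to change.** - Test the hypothesis with one yes/no per person: at least one 24 h quit attempt reported at any of the 3-, 6- or 12-month assessments. Count reported abstinence at a follow-up as an attempt, since everyone smokes at entry.
- Analyse it with a logistic model of condition and the stratification factors (stage of change, daily vs non-daily smoking), without abstinence status as a covariate.
- Say what the two quit-attempt models are.
- If interval results are also reported, state how participants abstinent throughout an interval are coded, and include assessment point in the model.

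The cost is wording and one derived variable from data already being collected. The downside is that a cumulative outcome needs a stated rule for missed interim surveys, and this matters because Power calculation allows for 50% attrition at each time point.

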### Study procedure

Informed consent is obtained from all study participants in accordance with the Helsinki Declaration and approved by the UCSF Committee in Human Research (#11-06294). During the informed consent process, participants’ understanding of the information provided is assessed through a series of multiple choice questions with required responses before being able to proceed with the study. Questions are based on those used in studies with potentially vulnerable populations [41, 42]. Any wrong answers during the consent process are sent to study staff who then contact a potential participant via email or Facebook for further clarification of the consent process. Therefore, no participant will be enrolled that has not answered all consent questions correctly. Participants consenting to participate in the study are asked to verify age by sending proof through email or social media. Verified participants are emailed a baseline assessment. Those completing the baseline assessment are randomized to receive either the Tobacco Status Project (TSP) intervention of referral to the Smokefree.gov website (control).

A stratified random assignment program was developed and participants are assigned from within stratified blocks immediately after completing the baseline assessment. Participants are stratified on stage of change (precontemplation, contemplation, preparation) and smoking pattern (daily vs. non-daily), variables known to be related to outcomes and addressed by the intervention [43]. Participants in the TSP group are assigned to “secret” (private) Facebook groups based on their readiness to quit tobacco. Groups begin when there are approximately 10 participants enrolled, as that has been deemed the optimal number based on analyses of engagement in our previous work [37] ([name], [name], [name]: Smoking cessation intervention on Facebook: Which content generates the best engagement?, submitted). Participants in the control condition are given a referral to the Smokefree.gov program and are encouraged to use it as much as they would like.

Assessments occur online using the survey program Qualtrics at baseline, 3, 6, and 12 months follow-up. Participants receive their choice of gift cards in the amount of $20 per assessment, and a $20 bonus for completing all three assessments, for a total possible stipend of $100 for completing all assessments.

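### The abstinence-goal outcome can already be met at entry, yet the baseline goal is not named as a covariate; the comparison stays valid but loses precision

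*Protocol article*

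**What the plan says.** All references are to the protocol article.

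- **Hypothesis** (Aims and hypotheses, Main Aim): the intervention arm will show "increased commitment to abstinence at 3-, 6-, and 12-months follow-up than those in the control condition".
- **Outcome** (Secondary outcomes, Abstinence goal): the goal is classed as none, intermediary or total abstinence. "Outcome will be measured as proportion endorsing a goal of abstinence at each timepoint".
- **Model** (Secondary analyses): commitment to abstinence is a yes/no response modelled over 3, 6 and 12 months. "Independent variables in all models will be treatment condition, abstinence status, and covariates identified as relevant to smoking characteristics in the literature".
- **Collection**: the Secondary outcomes section opens with "The following secondary outcomes will be assessed at each timepoint", and Overview of design says "Assessments are conducted online at baseline, 3-, 6-, and 12-months follow-up". Together these suggest that the goal is recorded at baseline.
- **Design** (Study procedure): randomisation is stratified on stage of change and on daily versus non-daily smoking.
- **Other covariates** (Primary analyses): a variable is controlled for if the preliminary analyses show a difference on it.

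**The concern.** Abstinence goal is the only between-arm secondary outcome that a participant can satisfy on the day of randomisation. The 50% reduction is calculated against baseline consumption. Quit attempts are counted since the previous assessment. Action or maintenance stage cannot be met at entry, because entrants are current smokers classed as precontemplation, contemplation or preparation. A person who enters wanting total abstinence and still wants it at 12 months, however, scores the same as one who came to want it during the trial.

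The earlier value of a yes/no outcome is usually a strong predictor of the later one. If it is left out of the model, explainable variation stays in the comparison, and people who cannot move upward dilute the effect in those who can. A real effect on commitment could then be missed although the data to sharpen the test are probably in hand. The model statement names abstinence status, which for trial entrants can only be a follow-up measurement, but not the outcome's own baseline value.

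**Working it through.** The article states no rate, effect size or power for this outcome, so there is no figure to reproduce. The calculations below are illustrations; every goal rate in them is an assumption.

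**Inputs from the article.** 480 randomised; 50% attrition at each time point (Power calculation). With 1:1 allocation (assumed), 480 × 0.5 / 2 = 120 observed per arm.

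**1. Dilution.** Let b be the share holding a total-abstinence goal at entry. Assume that 90% of holders keep it in both arms, and that non-holders adopt it at 20% (control) or 35% (intervention), a 15-point effect. Then

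- control proportion = 0.9b + 0.20(1 − b)
- intervention proportion = 0.9b + 0.35(1 − b)
- difference = 0.15(1 − b)
- share of control successes who held the goal at entry = 0.9b / control proportion

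| b | Control | Intervention | Difference | Control successes who were holders at entry |
|---|---|---|---|---|
| 10% | 27.0% | 40.5% | 13.5 points | 33% |
| 20% | 34.0% | 46.0% | 12.0 points | 53% |
| 30% | 41.0% | 51.5% | 10.5 points | 66% |
| 50% | 55.0% | 62.5% | 7.5 points | 82% |
| 70% | 69.0% | 73.5% | 4.5 points | 91% |

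**2. Power and type I error.** Same rates, 120 per arm, one follow-up time, two-sided .05, 2000 simulated trials per setting. The unadjusted two-proportion test is set against a Mantel-Haenszel test stratified on baseline goal.

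| b | Power, unadjusted | Power, adjusted | Type I error, unadjusted | Type I error, adjusted |
|---|---|---|---|---|
| 30% | 0.37 | 0.52 | .045 | .057 |
| 50% | 0.23 | 0.35 | .047 | .052 |

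The simulation omits stratification on stage and uses a simpler test than the planned mixed-effects logistic model. It shows the direction and rough size of the gain, not the power of the planned analysis.

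**3. Chance imbalance under milder persistence.** Assume that 70% of holders and 30% of non-holders endorse the goal at follow-up.

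- SE of the baseline difference = √(2b(1 − b)/120): 5.9 points at b = 30%, 6.5 points at b = 50%.
- One such SE moves the follow-up difference by (0.70 − 0.30) times that: 2.4 and 2.6 points.
- The follow-up proportion is 0.7b + 0.3(1 − b) = 42% and 50%, so the SE of the arm difference is √(2 × 0.42 × 0.58/120) = 6.4 points and √(2 × 0.5 × 0.5/120) = 6.5 points.
- The shift is therefore about 0.4 of one standard error of the comparison.
- The squared baseline to follow-up correlation is 0.4² × b(1 − b)/[p(1 − p)], with p the follow-up proportion: 0.16 × 0.21/0.2436 = 14% at b = 30%, and 0.16 × 0.25/0.25 = 16% at b = 50%. This is the variance that adjustment would remove in a linear model; it does not carry over directly to a logistic one.

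Stratification on stage would make the imbalance in step 3 smaller, to an extent that cannot be computed from the article.

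**The case against.** Read whole, the hypothesis ends by comparing the intervention with the control condition. A reader might infer from the word for increase that it promises change from baseline and so contradicts an outcome measured only at follow-up. The text does not support that: a between-arm difference in follow-up proportions answers the hypothesis as written. Keeping a total-abstinence goal for 12 months is also a legitimate success for an outcome defined as holding that goal.

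A reader might also infer that counting baseline holders as successes biases the result. It does not. Randomisation makes holders equally expected in both arms, stratification on stage probably tightens this, and the unadjusted type I error was near .05. The 2.4 to 2.6 point shift is ordinary sampling error that a valid confidence interval already covers.

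Nor do the documents exclude the baseline goal from the model. The covariate list is open to literature-based variables, the preliminary analyses may add others, and a statistical analysis plan that is not shown may settle the matter.

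All of this stands, and it limits the point to one of efficiency. It does not remove it. A goal about quitting is not clearly a smoking characteristic. The rule on noted differences sits under the primary analyses and acts only when a difference appears, which makes adjustment depend on the data and forgoes the gain in precision otherwise. Balance at randomisation also does not guarantee balance among those observed when half may be lost and one planned analysis uses those who stay in the study. If entry goal predicts retention differently by arm, conditioning on it helps.

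**Conclusion.** The point holds as one of dilution and lost precision in a secondary outcome, with some exposure to imbalance among those retained. It is neither a contradiction with the hypothesis nor a systematic bias, and the accurate description is that the baseline goal is not named, not that it is left out. One limit on interpretation follows: the follow-up proportion alone cannot show that individuals' commitment rose.

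Under the stated assumptions, with 30% to 50% holding the goal at entry, a 15-point effect among non-holders appears as 10.5 to 7.5 points, and adjustment raises power by 15 and 12 percentage points (0.37 to 0.52; 0.23 to 0.35). If few enter with the goal the issue is small; at 10%, the difference is still 13.5 points. The conclusion that adjustment is worthwhile rests on the goal being recorded at baseline and persisting to a fair degree. The article implies the first and does not address the second.

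**What to change.** In Secondary analyses, name baseline abstinence goal (total abstinence versus other) as a fixed covariate in the commitment-to-abstinence model, and state that it is included whether or not the arms differ on it at baseline. State in the outcome definition that the goal is recorded at baseline.

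Optionally, add a descriptive table by arm of the proportion adopting a total-abstinence goal at 3, 6 and 12 months among those without it at entry. Adjustment improves precision but does not undo the dilution; this table would show the effect where movement is possible. It answers a narrower question than the hypothesis and should be labelled descriptive.

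The cost is one covariate and, if wanted, one table, with no change to assessments if the goal is collected at baseline as the article suggests. If the statistical analysis plan already names the covariate, nothing further is needed in the model.
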